## Abstract

**Background:**

Diabetic kidney disease (DKD) is the main cause of end-stage kidney disease and has become a heavy economic and social burden due to its high prevalence and morbidity. The most effective strategy is that patients with DKD should be diagnosed and treated early. Preliminary studies showed that the Chinese herbal Tangshen Formula (TSF) may delay the progression of DKD, reducing microalbuminuria and macroalbuminuria and improving renal function. We designed a randomized, double-blind, placebo-controlled trial to evaluate the efficacy of TSF in patients with DKD.

**Methods/design:**

This trial is a 13-center, randomized, double-blind, placebo-controlled study. A total of 632 participants will be randomized in a 1:1 ratio to an experiment group (TSF plus losartan) and a control group (placebo plus losartan). The trial cycle will last 24 weeks. The primary outcome will be the change in the urine microalbumin–creatinine ratio from baseline to week 24. The secondary outcome will be the change in the rate of progression to the clinical proteinuria period after intervention, the rate of urine microalbumin negative conversion, the rate of normal urinary microalbumin, the doubling rate of the baseline creatinine value and the glomerular filtration rate between the two groups. Safety in medication will also be evaluated.

**Discussion:**

We hypothesize that patients with type 2 diabetes in the early stage of DKD will benefit from TSF. If successful, this study will provide evidence-based recommendations for clinicians.

**Trial registration:**

ClinicalTrials.gov, NCT03009864. Registered January 2017.

## Background

Diabetic kidney disease (DKD) is the most common diabetic microvascular complication and the primary cause of end-stage kidney disease (ESKD). Pooled data from 54 countries revealed that more than 80% of ESKD arises from diabetes, hypertension or a combination of both. The prevalence of ESKD was also up to 10 times higher in people with diabetes than in those without [1]. Several studies showed that 20% of people with diabetes from the UK [2] and 40% of individuals with diabetes in the USA will develop chronic kidney disease (CKD), whereas 19% show signs of DKD stage 3 or higher [3]. It is responsible for 40% of patients experiencing dialysis after diagnosis of diabetes mellitus in the developed world [4]. Moreover, there has also been a continuous increase in the incidence of ESKD due to the increasing incidence of T2DM, notably in China, with 11.9% from the high incidence of type 2 diabetes [5]. As impairment in renal function progresses, it is bound up with a high risk of mortality, cardiovascular events and hospitalizations [1] and is associated with a heavy economic burden, with estimated average annual healthcare costs ranging from $4573 to $10,322 [6]. Some risk factors of DKD have been identified, such as ageing, hypertension and hyperglycemia [7, 8]. Current strategies for DKD aim to delay deterioration of renal function through actively controlling glucose, blood pressure and blood lipid levels, and via restraint of the renin–angiotensin–aldosterone system (RAAS) [6–8], such as using angiotensin-converting enzyme inhibitors (ACEIs) and angiotensin II receptor blockers (ARBs).

However, these therapies are difficult to achieve in all patients with DKD and stable results in the long term as well as these treatments may not reverse DKD [9, 10], and even with treatment using currently effective therapies, ESKD will finally occur in a proportion of patients, requiring a dialysis regimen and kidney transplant. Therefore, the most effective strategy is that kidney disease in patients with diabetes should be diagnosed and treated early. Patients with type 2 diabetes with microalbuminuria are at high risk of progression to overt renal disease, indicating that those patients easily enter the stage of clinical diabetic nephropathy (stage 4 or 5). In addition, not only ESKD but also premature cardiovascular events are predicted by microalbuminuria in diabetes [11–13], whereas effective intervention therapies for microalbuminuria could improve clinical outcomes in DKD.

Although ACEIs or ARBs showed evidence for decreasing microalbuminuria in patients with type 2 diabetes and nephropathy [14, 15], some adverse events (cough, rhinitis, hyperkalemia, acute kidney injury and angioedema) related to ACEIs or ARBs might cause poor adherence [1–16]. Therefore, it is imperative to seek effective renoprotective therapies.

Chinese herbal medicine (CHM) has long been widely used in China [17]. Numerous studies have demonstrated the biological activity and therapeutic mechanism of CHM [18–21]. Recent studies show that certain Chinese herbs have renoprotective effects, improving the glomerular filtration rate (GFR) and decreasing proteinuria, especially in patients with microalbuminuria [22–26]. This study is designed to investigate whether Tangshan Formula (TSF) may represent a potential remedy for slowing disease progression in early type 2 diabetic nephropathy. If positive, this work may provide an evidence-based medicine remedy for slowing or preventing the clinical progression of DKD.

## Methods/design

### Study design

This protocol will be designed as a randomized, placebo-controlled and multicenter trial. Participants, investigators and statisticians will be blinded. A total of 632 subjects will be recruited at the following 13 tertiary A hospitals in mainland China: Guang An Men Hospital of the China Academy of Chinese Medical Sciences, The First Affiliated Hospital of Anhui University of Traditional Chinese Medicine, Beijing Hospital of Traditional Chinese Medicine, Hubei Hospital of Traditional Chinese Medicine, Zouping County Hospital of Traditional Chinese Medicine, Zibo Wanjie Hospital and Shijiazhuang Hospital of Traditional Chinese Medicine, Zhengzhou City Hospital of Traditional Medicine, Xingtai City Hospital of Traditional Medicine, Shexian Country Hospital of Traditional Medicine, Baoding City of Hospital of Traditional Medicine, Yantai Bai shi Hospital of Traditional Medicine and Jilin Province Hospital of Traditional Medicine. The trial will be implemented base on the principles of good clinical practice and reported according to the CONSORT statement [27, 28]. The trial flow diagram is illustrated in Fig. 1. The Standard Protocol Items: Recommendations for Interventional Trials (SPIRIT) [29] Checklist is shown in Additional file 1. This study has been registered at ClinicalTrials.gov (NCT03009864).

**Fig. 1 Fig1:**
[figure not shown]
Flow diagram of enrollment, intervention and assessments. TSF Tangshen Formula

### Participants

#### Diagnostic criteria

The diagnostic criteria for this trial will be set based on the American Diabetes Association guidelines [7], Chinese Diabetes Society guidelines [8], National Kidney Foundation Kidney Disease Outcomes Quality Initiative (NKF-KDOQI) guidelines [30] and Kidney Disease Improving Global Outcomes (KDIGO) 2012 Clinical Practice Guideline [31]. For a diagnosis of early-stage DKD, patients with DM will have to present the following conditions:
Diagnosed with type 2 diabetesPatients with type 2 diabetes with microalbuminuria and urinary microalbumin excretion rate (UAER)
For microalbuminuria, two repeated tests performed within 6 months will need to produce abnormal resultsUAER of 30–300 mg/24 h or urinary albumin-to-creatinine ratio (ACR) of 30–300 mg/g (mg/mmol)Have clinical manifestations of kidney diseases, such as edema, anemia, renal dysfunction, etc.

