### Outcomes

#### Primary outcomes

Urinary microalbumin (MAlb) is a critical indicator for the diagnosis of early renal impairment in diabetes mellitus. For early-stage DKD, the urinary microalbumin–creatinine ratio (ACR) will be a primary evaluation index. The change in ACR from baseline will be evaluated between the two groups, and the ACR will be compared at baseline and treatment endpoint (24 weeks) in each group.

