### Bias analysis

The main evaluation outcome of this trial is the rate of progression from microalbuminuria into clinical proteinuria, which is very objective. Although ACEI and ARB drugs have achieved a recognized efficacy internationally, a certain proportion of patients still cannot delay the progression of DKD even using these two drugs. Therefore, the bias factors affecting the outcome evaluation include three aspects: blood glucose level; ACEI and/or ARB use; and laboratory testing error for urine microalbuminuria.

These factors are solved as follows: for the blood glucose level, the consistency of this factor in the two groups is ensured due to the random and double-blind study design method; subjects only take losartan and no other ARB or/and ACEI drugs; and central laboratories are used for the main outcomes.

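### The ACR entry range of 30–300 is printed against both mg/g and mg/mmol, units that differ about 8.84-fold; mg/g is evidently meant, and the line needs a minor correction

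*Protocol article*

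**What the plan says.** Under Participants, Diagnostic criteria, the protocol article requires microalbuminuria shown by two abnormal tests within 6 months. It gives two alternative measures joined by *or*: a urinary albumin excretion rate (UAER) of 30–300 mg/24 h, or a "urinary albumin-to-creatinine ratio (ACR) of 30–300 mg/g (mg/mmol". The bracket then closes with no numbers of its own.

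The Inclusion criteria ask for DKD with microalbuminuria and add no figure. The Exclusion criteria set no upper limit on albuminuria. The numeric ACR threshold therefore stands in this one place.

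The same ratio is the primary outcome: "The change in ACR from baseline will be evaluated between the two groups". Progression to clinical proteinuria is a secondary outcome. On measurement, the Bias analysis section states that "central laboratories are used for the main outcomes".

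**The concern.** Milligrams of albumin per gram of creatinine and per millimole of creatinine are different scales, so a range that is right on one is wrong on the other. A bracketed second unit would normally carry its own converted limits. Here it stands bare beside limits that fit only the first unit.

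The threshold decides who enters. If it were applied in the bracketed unit, patients well above the microalbuminuria range could qualify by ACR. Two outcomes would suffer:

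- Someone already in clinical proteinuria at entry cannot validly be counted as progressing to it.
- The ACR change of such a patient, measured on the raw scale, would be large beside that of the intended population and would add variance to the primary comparison.

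**Working it through.** **Inputs**

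- Printed range, 30–300, with mg/g first and mg/mmol in brackets (Diagnostic criteria).
- Parallel criterion, UAER 30–300 mg/24 h (same section).
- Normal limit for urinary microalbumin, below 20 μg/min (Secondary outcomes).
- Molar mass of creatinine, M = 113.12 g/mol. The article does not give it, so it is an assumption, varied here from 113.0 to 113.2.

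**Step 1: conversion factor.** 1 mg/mmol = 1000/M mg/g = 1000/113.12 = 8.84 mg/g. Over the range of M the factor runs from 8.83 to 8.85, so the choice of M does not matter.

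**Step 2: the range on each scale**

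| Reading | In mg/g | In mg/mmol |
|---|---|---|
| 30–300 mg/g | 30–300 | 30/8.84 = 3.4 to 300/8.84 = 33.9 |
| 30–300 mg/mmol | 30 × 8.84 = 265 to 300 × 8.84 = 2652 | 30–300 |

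The printed equivalence is not reproduced. The two readings overlap only from 265 to 300 mg/g.

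**Step 3: how much of the mg/mmol reading lies above the ceiling.** (2652 − 300)/(2652 − 265) = 2352/2387 = 98.5% of its width. This is a share of the interval, not of patients, because the article gives no ACR distribution.

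**Step 4: which reading is intended.** The UAER criterion uses the same numbers, 30–300, on the mass scale. The normal limit of 20 μg/min equals 20 × 1440/1000 = 28.8 mg/24 h, close to the lower UAER limit of 30. Both fit mg/g, as does the word microalbuminuria.

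**Step 5: illustration of the consequence.** A patient at 100 mg/mmol falls inside the bracketed reading and has 100 × 8.84 = 884 mg/g, almost three times the ceiling. A 20% fall in ACR is then 0.20 × 884 = 177 mg/g, against 0.20 × 100 = 20 mg/g for a patient at 100 mg/g.

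**The case against.** The strongest reply is that no careful reader would be misled. The leading unit is mg/g, the bracket carries no numbers, the UAER limits agree with mg/g, and a patient at 884 mg/g does not have microalbuminuria, which the Inclusion criteria require. Training to a standard manual and a monitor who checks entry criteria give further protection (Quality control data collection). Most of this stands: it settles the intended meaning and keeps the point minor. It does not make the printed line correct.

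Central laboratories help as well. Table 1 has a single screening/baseline column, so the ACR taken there is plausibly also the baseline of the primary outcome and reported in one unit. But the article promises central testing for the main outcomes and does not mention screening. The screening visit covers only days –7 to 0, while the two qualifying tests may be spread over 6 months, so qualifying results may come from earlier tests done elsewhere.

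Four stronger readings are tempting, and the article supports none of them.

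- *Macroalbuminuric patients will be, or have been, enrolled.* Nothing shows that any of the 13 sites reports ACR in mg/mmol.
- *True microalbuminuric patients would be turned away.* UAER and ACR are alternatives, so a patient at 30–265 mg/g could still enter through UAER, which Table 1 schedules for everyone at screening.
- *The treatment comparison would be biased.* Any wrong entry would precede blinded 1:1 allocation and so should fall on both arms. The effect would be on the population, the variance and the validity of the progression outcome. Statistical analysis also allows the Wilcoxon rank-sum test, which would lessen the weight of extreme changes.
- *The primary outcome is defective because it states no unit.* An article may leave a reporting unit to the full protocol or analysis plan.

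**Conclusion.** The entry line is wrong as printed: one range is attached to two units that differ by a factor of about 8.84. This rests only on the molar mass of creatinine and is insensitive to its exact value. The intended threshold is evidently 30–300 mg/g.

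The harm is conditional. It needs a site to apply the bracketed unit; the ACR route would then admit values up to about 2652 mg/g, and no other numeric limit in the article would stop it. How many patients this could affect cannot be estimated, because the article reports neither the sites' units nor an ACR distribution. The factor of 8.84 is a conversion error, not an estimated effect on the trial's result.

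Severity is minor: a one-line correction to an operative threshold.

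**What to change.** 1. In Diagnostic criteria, delete the bracketed mg/mmol, or print its equivalent beside the existing limits: 30–300 mg/g (about 3.4–34 mg/mmol).
2. Record the ACR unit with every value in the electronic data capture system, and convert to one unit for eligibility, baseline and outcome.
3. Check the unit behind the qualifying ACR of patients already enrolled. The article reports 95 of 632 recruited at submission (95/632 = 15%), so most enrolment could still be protected at that point.

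The cost is a one-line amendment, a unit field with a check in the database, a short note to sites and a limited review of qualifying results. Sample size, design and analysis are unaffected.

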#### Inclusion criteria

Patient diagnosed with DKD with microalbuminuriaAge 30–70 yearsSigned informed consent

#### Exclusion criteria

Proteinuria caused by non-DKD in the patient, such as gout, primary hypertension, tumors and proteinuria caused by chronic kidney diseaseCardiovascular, liver, kidney, hematopoietic system or other primary severe disease; serum transaminase more than double the standard value; serum creatinine (SCr) higher than the upper limit of normal; and psychiatric patientsPregnancy, preparation for pregnancy or lactation, or any history of drug allergyThe patient developed renal failure (anemia and uremia)Participation in another clinical trial or use of any other drug within the previous monthRecent use of ACEIs or ARBs except losartan in the past 1 monthAny excessive consumption of alcohol or any consumption of psychoactive substances, drug abuse or drug dependence during the past 5 yearsAccording to the researcher’s judgment, as some other diseases or conditions reduce the possibility of enrollment or complicate the enrollment, such as frequent changes of jobs and an unstable living environment, which may easily lead to loss of visits

### Randomization and concealment

A specific randomization sequence will be computer generated by a computerized random number generator from an independent clinical research organization (CRO) of the Institute of Clinical Medicine of the Chinese Academy of Chinese Medical Sciences, which is not involved in the study. All eligible patients will be randomized to the experimental group or the control group at a 1:1 ratio. An independent non-investigator will protect the concealment list. The medical information will be confidential and not be available to any investigator for the duration of the study. If a medical emergency occurs, the individual’s randomization code and group allocation can be identified.

### Blinding

This study will be designed as double-blind. Not only are subjects and investigators blinded in these trials, but drug administration, statisticians and curative evaluators are also masked. Treatment allocation will be uncovered after completion of the study. In addition, TSF and placebo cannot be distinguished by their taste, smell and appearance. After production, study drugs will be packaged and transferred to numbered bottles by designated pharmacists in accordance with the randomized list. No one can tell the difference except the person who is in charge of concealment.

### Intervention

All subjects in the two groups will receive the conventional treatment, including oral losartan (50 mg/once a day), diet, exercise and oral medicine, to ensure access to steady levels of blood glucose, blood lipids and blood pressure, based on the recommendations of the American Diabetes Association guidelines [7] and Treatment of Chinese Diabetes Society guidelines [8]. Subjects will be randomly assigned to receive placebo (6 g/bag twice per day) or Tangshan Formula (6 g/bag twice per day) by specified sequence number from the central randomization system. The treatment will last for 24 consecutive weeks.

### Outcomes

#### Primary outcomes

Urinary microalbumin (MAlb) is a critical indicator for the diagnosis of early renal impairment in diabetes mellitus. For early-stage DKD, the urinary microalbumin–creatinine ratio (ACR) will be a primary evaluation index. The change in ACR from baseline will be evaluated between the two groups, and the ACR will be compared at baseline and treatment endpoint (24 weeks) in each group.

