### Study visits and assessment

The intervention cycle will be 24 weeks, including a run-in period. After the research commences, visits will occur every 4 weeks during the study period. An overview of specific measurements and time points for data collection is presented in Table 1.

**Table 1 Tab1:** Measurement items and point of data capture

Visit project	Screening period/baseline	Visits 1–2, 4–5	Visit 3	Visit 6
Visiting time	–7 to 0 days	Medication 4, 8, 16, 20 weeks ±7 days	Medication 12 weeks ±7 days	Medication 24 weeks ±7 days
Collect basic medical history				
Sign informed consent	×			
Fill in general information	×			
Medical history and treatment history	×			
Determine inclusion and exclusion criteria	×			
Vital signs	×	×	×	×
Physical examination	×	×	×	×
Comorbidity and medication records	×	×	×	×
Monitoring and inspection				
Urine pregnancy test	×			
Glycosylated hemoglobin, blood lipids	×		×	×
Fasting blood sugar and blood pressure	×	×	×	×
Effectiveness observation				
Urinary microalbumin–creatinine ratio	×	×	×	×
Urinary microalbumin excretion rate	×	×	×	×
Serum creatinine	×	×	×	×
Glomerular rate filtration	×	×	×	×
24-h urinary microalbumin and 24-h urinary microalbumin quantification	×		×	×
Physico-chemical examination				
Routine blood test and routine urine test	×		×	×
Stool routine examination	×		×	×
Vital signs	×	×	×	×
ECG, liver and kidney function	×		×	×
Adverse event		×	×	×
Other work				
Random grouping	×			
Distribute drug and patient journal cards	×	×	×	
Recovery drugs, quantity statistics		×	×	×
Recycle patient’s diary card		×	×	×
End of study summary				×

*ECG* electrocardiogram

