### Sample size

The sample size was estimated according to the relevant data from the losartan study published in *New England Journal of Medicine* [32, 33]. These results showed that the proportion of patients with the ACR reduced by 50% or more in the losartan group was 12.5% and the preliminary study of TSF data manifested that TSF as an add-on study can improve 50% of patients. The estimated proportion of patients with the ACR reduced by 50% or more was 18.7%. The estimated sample size formula was tested using the hypothesis of two population rates:
$$ n={\frac{\left[ u\alpha \sqrt{2p\left(1-p\right)}+ u\beta \sqrt{p1\left(1-p1\right)+p2\left(1-p2\right)}\right]}{{\left(p1-p2\right)}^2}}^2 $$

where *n* is the sample size; *p*_1_ and *p*_2_ are the sample rates, and *p* = (*p*_1_ + *p*_2_) / 2 is the sample average rate; and *α* is the type 1 error and *β* is the type 2 error, while *u*_*α*_ and *u*_*β*_ are the locus of the corresponding standard normal distribution. According to the unilateral test, *u*_*α*_ = 1.64485 and *u*_*β*_ = 0.84162, and substituting these into the formula presents *n* = 274.46. Therefore, 275 patients were needed in each group. Considering a dropout rate of no more than 15%, the final sample size was estimated to be 632 in total.

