### Statistical analysis

The statistical analysis of this study was completed by an independent statistician, and the detailed statistical analysis plan was formulated separately by a statistician before the inception of this trial and determined with the Principal Investigator. Three analysis sets will be used for assessment of this study: the intention-to-treat set (ITT), the per-protocol analysis set (PPS) and the safety analysis set (SAS). The ITT and PPS will be used to appraise the efficacy of TSF. If any given case exists missing a critical variable, the last observation used as the final results will be carried forward to the final data. The changes of urinary microalbumin–creatinine ratio, urinary microalbumin, GFR, creatinine and baseline information will be present after treatment. A paired *t* test or the Wilcoxon signed-rank test will be employed to compare each group. Changes relative to baseline after treatment will be compared between groups using the *t* test or the Wilcoxon rank-sum test. *P* < 0.05 will be deemed to show a statistically significant difference.

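### The within-arm baseline-to-week-24 ACR test, listed unranked under the primary outcome, cannot isolate a TSF effect; the between-arm test is valid but gives up modest precision (minor)

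*Protocol article*

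**What the plan says.** **Outcome and tests.** Primary outcomes names two things in one sentence: the change in ACR compared between the groups, and that "the ACR will be compared at baseline and treatment endpoint (24 weeks) in each group". Neither is ranked above the other. Statistical analysis gives the within-group comparison a paired t test or a signed-rank test ("Wilcoxon signed-rank test will be employed to compare each group") and the between-group change a t test or rank-sum test. One 0.05 threshold covers both, and no baseline covariate is named.

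**Background treatment.** Intervention states: "All subjects in the two groups will receive the conventional treatment, including oral losartan (50 mg/once a day"), together with "diet, exercise and oral medicine, to ensure access to steady levels of blood glucose, blood lipids and blood pressure". Exclusion criteria bars recent use of other ACE inhibitors and ARBs but exempts losartan. Prior losartan is thus allowed and not required.

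**Timing.** In Table 1 the baseline ACR and randomisation fall in the screening column, day -7 to 0. The text above the table counts a run-in inside the 24 weeks, but the table shows no run-in column. At screening the table lists "Medical history and treatment history" and "Comorbidity and medication records".

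**Entry and planning.** Diagnostic criteria selects on ACR or UAER of 30-300, with two abnormal tests within 6 months. Sample size states that "the proportion of patients with the ACR reduced by 50% or more in the losartan group was 12.5" per cent and, for the TSF arm, "The estimated proportion of patients with the ACR reduced by 50% or more was 18.7" per cent.

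**The concern.** A before-after test within the TSF arm answers whether ACR changed, not whether TSF changed it. Three other things can move ACR over the 24 weeks:

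- the diet, exercise, glucose, lipid and blood pressure treatment given to everyone;
- losartan, for those who begin it at entry (the Background section itself says ACE inhibitors and ARBs lower microalbuminuria);
- regression to the mean, if the baseline value is one of the qualifying tests.

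The safeguards in Bias analysis (randomisation with blinding, losartan as the only such drug, central laboratories) protect the contrast between arms. They do nothing for a test that leaves the control arm out.

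At stake is how a result could be reported. A significant fall in the TSF arm could be presented as a primary finding although the between-arm difference is null. A smaller matter is that the named between-arm test leaves unused the baseline ACR that the trial collects.

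**Working it through.** **1. The protocol's own figures.** The TSF rate follows from a 50% relative improvement on the losartan rate: 12.5% x 1.5 = 18.75%, given as 18.7%. Share of TSF-arm falls of 50% or more expected without TSF: 12.5/18.7 = 0.668, or 67%. Part attributed to TSF: 18.7 - 12.5 = 6.2 points. These are responder proportions; they do not translate directly into a paired test of mean or median change.

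**2. Inputs for the rest.** n = 275 per arm is the stated number before dropout, used here only as the planned analysed number. (The printed formula with the stated rates gives 422.5, not 274.46. That is a separate matter.) Everything else is assumed: log scale, two-sided 0.05, SD of change in log ACR 0.6 to 1.0.

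**3. Fall from any cause that makes the within-arm test significant.** Fall = 1 - exp(-k x SD/√275), with k = 1.96 for a 50% chance and 2.802 for 80%.

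| SD | 50% chance | 80% chance |
|---|---|---|
| 0.6 | 6.8% | 9.6% |
| 0.8 | 9.0% | 12.6% |
| 1.0 | 11.1% | 15.5% |

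**4. Losartan starters, no TSF effect (illustration).** Share s starts losartan with log change d. Mean m = s·d, variance v = SD² + s·d² - m², z = |m|/√(v/275).

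- Half start, 30% fall, SD 0.8: d = ln 0.7 = -0.357; m = -0.178 (a 16% fall); v = 0.672; z = 3.61; significant in 95% of trials.
- As above, with 10% of patients stepped down to 50 mg and rising 15%: 15% fall, 91%. With 20% stepped down and rising 20%: 13% fall, 81%.
- A quarter start, 20% fall, SD 1.0: m = -0.056 (a 5% fall); v = 1.009; z = 0.92; 15%.

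**5. Regression to the mean alone (illustration).** Simulated log ACR, between-patient SD 0.9, within-patient SD 0.57, two tests in 30-300, the second taken as baseline.

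| Source geometric mean (mg/g) | Change in ACR | Within-arm test significant |
|---|---|---|
| 20 | -18% | 99% |
| 40 | -10% | 67% |
| 95 | 0% | 5% |
| 150 | +6% | 24% |
| 200 | +10% | 54% |

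The sign turns at the log midpoint of the window, √(30 x 300) = 94.9 mg/g.

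**6. Both tests side by side, no TSF effect.** 20,000 simulated trials, SD 0.6, with the same background fall in both arms.

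| Background fall | TSF arm significant | TSF arm significant, placebo arm not | Between-arm test significant |
|---|---|---|---|
| 5% | 29% | 20% | 5.0% |
| 10% | 82% | 14% | 5.1% |
| 20% | >99.9% | 0% | 5.1% |

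**7. Precision of the between-arm test.** With baseline restricted by the entry window, the ratio of ANCOVA variance to change-score variance is 0.89 to 0.94 in the assumed cases. Power where the change-score test has 80%: Φ(2.802/√ratio - 1.96) = 84% at 0.89 and 82% at 0.94. A wider set of assumptions (ratio 0.87 to 0.975) gives 85% to 81%.

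Entry losartan use as a covariate, half starters, 30% fall, SD 0.8: v/SD² = 0.672/0.64 = 1.05, so 80% adjusted is Φ(2.802/√1.05 - 1.96) = 78% unadjusted. It is 79% with 10% or 90% starters, and there is no loss at 0% or 100%.

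**The case against.** The strongest reply is that the trial's inference is not damaged. The between-arm comparison comes first in Primary outcomes, the sample size rests on comparing two rates, and the design is randomised, blinded and placebo-controlled. The within-arm test is run in both groups, so a background fall should also show under placebo. This largely stands and is why the point is minor. It does not close the gap: in step 6 the TSF arm alone reaches significance in 20% or 14% of null trials when the background fall is 5% or 10%.

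A second reply is that covariates and transformation belong in the separate analysis plan, which is not shown. That is fair for detail, but the article itself names unadjusted tests on change, and it is that stated choice which costs precision.

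Third, nearly all the sizes in steps 3 to 7 are assumed. That stands; they illustrate and do not estimate.

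A reader might infer more than the text supports:

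- **That the TSF effect is confounded with losartan.** It is not: both arms receive it, and the between-arm test holds its 5% level.
- **That a within-arm P value will be used to claim efficacy.** The protocol does not say so; it only fails to rule it out.
- **That every patient starts losartan with study drug.** Prior users are allowed, the share is not given, and the ambiguous run-in might stabilise dosing.
- **That regression to the mean must flatter TSF.** It can raise ACR as well as lower it, and it arises only if baseline is a qualifying test, which is not stated.

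**Conclusion.** The point holds, at minor severity. A before-after test that cannot separate TSF from concurrent care stands unranked under the primary outcome at the same 0.05 threshold as the valid comparison. The only size resting on the document alone is the 67% of TSF-arm halvings of ACR expected without TSF. Within-arm rejection rates under no TSF effect run from 5% to over 99% across the assumed inputs, so they show that the test can mislead, not how often it would. Regression to the mean spans about an 18% fall to a 10% rise for assumed source geometric means of 20 to 200 mg/g.

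The between-arm test is valid under randomisation with complete data. Its cost is precision only: about 2 to 4 power points at 80% from leaving out baseline ACR, and at most about 2 from leaving out entry losartan use in the assumed central case.

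**What to change.** State that the between-arm comparison is the sole primary test, analysed by ANCOVA on log week-24 ACR with baseline log ACR as covariate. Label the within-arm baseline-to-week-24 tests descriptive and say that no TSF efficacy claim will be drawn from them.

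Optional: add entry losartan use (yes/no) as a further covariate, taken from the treatment history and medication records at screening. Table 1 does not say that dose is captured, so yes/no is enough. The gain is nil if entry use is uniform.

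Cost: wording and slightly more analysis work, with no extra patients, visits or data. The within-arm P values lose their primary standing. The article reports recruitment still under way and allocation masked until the study is complete, so the change can be made without knowledge of results by arm.
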